### Sample size

In each country (India and Nigeria), complete samples from a minimum of 30 women who receive the active drug to enable association of covariates (country, maternal age (years) weight (kg), maternal height (cm), BMI, gestational age, fetal sex) with PK parameters will be required.^25^ Given that all consenting women may not be able to provide the required samples—due to an estimated 30%–40% delivering within 12 hours of the first ACS dose or withdrawing consent—the sample size for each group has been increased by 60% to account for these potential losses, that is, 50 women per arm (DEXp or BETp or placebo) in each country, that is, 150 women from India and 150 women from Nigerian sites.

### Study procedures

Serial maternal blood samples will be collected starting before the administration of the first dose of IMP up to 96 hours after the last dose, through a dedicated indwelling cannula or by venipuncture. A cord blood sample will also be collected at birth. The sampling schedule is provided in table 1. All study sites will collect the samples at time points within the sampling time window depicted in table 1 (see online supplemental appendix table 1 for site-specific schedules). The sampling time points for the PK and PD analysis are indicated in table 1.

**Table 1 T1:** Blood sampling schedule

Sample number	Sampling time point	Maternal PK (BETp and DEXp)	Maternal PD (cortisol, glucose, WBC counts)	Cord PK+PD
1	*Baseline (−0.5 hours to 0 hours)*	√	√	
2	1–4 hours post first dose	√	√	
3	8–12 hours post first dose	√	√	
X*	At birth	√	–	√
4	24–36 hours after the last dose†	√	√	
5	48–60 hours after the last dose†		√	
6	72–96 hours after the last dose†		√	

PD parameters include serum cortisol, plasma glucose, total and differential WBC count (neutrophils, basophils and lymphocytes).

Windows for all draws ±30 min, except sample 6. Sample 6 to be drawn as close as possible to the stated time point for the site, otherwise at the point of discharge.

* Birth can happen at any time therefore, birth sample is not numbered sequentially and is labelled as X.

† Regardless of the time of birth.

BETp, betamethasone phosphate; DEXp, dexamethasone phosphate; PD, pharmacodynamics; PK, pharmacokinetics; WBC, white blood cell.

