#### Estimation method

The first-order conditional estimation method with the interaction option implemented in NONMEM 7.5 will be primarily considered. Alternatively, the importance sampling method will be used for parameter estimation if the primary method fails due to sparse data.

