#### Model building procedures

A base model will first be developed for the pretreatment and placebo measurements, the PK of each drug, and each PD biomarker using the models established by Krzyzanski *et al*.^28^ Once adequate base models have been developed, the joint drug/PD models and covariate effect models will be built. To ensure reasonable initial estimates, we will use the results from the Krzyzanski study.

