#### Fixed effects models

At stage 1, a two-compartment disposition model with first-order absorption will be used for describing plasma drug concentrations as the primary assessment (figure 2). Placebo cortisol data will be captured with the cosine circadian model. The inhibitory effect of the drugs on cortisol will be described by an indirect response model (figure 2).^29^ The cellular PD biomarkers will be described by inhibitory or stimulatory indirect response models that account for production (*k*_in_) and loss (*k*_out_) of the various biomarkers. Drug effects on plasma glucose will be described by a similar basic stimulatory indirect response model.

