#### Statistical analysis

Drug-related PK and PD individual parameters (eg, V, CL, ka, Emax, EC50) will be summarised using descriptive statistics. Two-way analysis of variance will be applied to test for between drug differences. The population estimates of PK-PD parameters will be compared using 95% CIs. For the model selection, the χ^2^ test for significance of the change in the maximum likelihood objective function will be used. For the selection of significant covariates, the likelihood ratio test will be applied.

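### Individual ka is to be summarised and apparently tested between drugs by ANOVA, but the sampling schedule informs it so weakly that the test would often show a spurious difference

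*Protocol article*

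**What the plan says.** **Sampling.** Table 1 (protocol article, Study procedures) ticks maternal PK at baseline, at "1–4 hours post first dose", at "8–12 hours post first dose", at birth (untimed) and at "24–36 hours after the last dose". The two later draws are for PD only. The tolerance reads "Windows for all draws ±30 min, except sample 6", so at the extreme sample 2 falls at 0.5 h and sample 3 at 7.5 h. No timed PK draw follows the second, third or fourth dose until 24 h after the last one.

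**Model.** Fixed effects models states: "At stage 1, a two-compartment disposition model with first-order absorption will be used for describing plasma drug concentrations as the primary assessment". That is five fixed effects per drug: ka, CL, central volume (V1), Q and peripheral volume (V2). The Abstract says a model will be developed for each drug.

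**Use of the earlier study.** Model building procedures takes over its model forms. For numerical values it says "To ensure reasonable initial estimates, we will use the results from the" earlier study; no fixed value and no prior is mentioned. If the main estimation method fails, "the importance sampling method will be used for parameter estimation if the primary method fails due to sparse data".

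**Reporting.** Statistical analysis states: "Drug-related PK and PD individual parameters (eg, V, CL, ka, Emax, EC50) will be summarised using descriptive statistics". The next sentence applies two-way ANOVA to look for differences between the drugs. The one after that compares population estimates through 95% CIs.

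**The concern.** ka is learned from samples taken while the drug is still being absorbed. Here one scheduled point per woman has to inform absorption, central volume and distribution together. Pooling over women helps the typical value somewhat, but it does little for an individual woman's ka.

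When a woman's data say little about her ka, her individual estimate falls back on the typical value for her drug. With a separate model per drug, the women in each arm then cluster tightly around one estimated number. An ANOVA sees a tiny within-arm spread and treats the two typical values as if they were known. A difference between them that is only estimation error is then declared significant. At stake is a published statement that the two steroids are absorbed at different rates, with no real evidence behind it.

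**Working it through.** **The plan's own figure.** Sample size asks for 30 women with complete samples and allows for 30–40% losses: 30 / (1 − 0.40) = 50 per arm per country, as stated (30 × 1.6 = 48 is within 2). Two countries give 100 women per drug. Reading the 30 as per drug per country gives 60 completers per drug. The article gives no precision figure for ka.

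**Precision of ka.** First-order population Fisher information was computed for the planned model with 12-hourly doses under Table 1. The PK values are assumptions, since the article gives none: ka 0.5–3/h, CL 8–12 L/h, V1 40–60 L, Q 5–15 L/h, V2 30–60 L, between-woman SD 0.30 on the log scale, residual error 15–25%. RSE is relative standard error. Shrinkage is 1 minus the ratio of the SD of the individual estimates to the between-woman SD.

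| Setting | RSE of ka | RSE of CL | Individual information on ka |
|---|---|---|---|
| 100 women per drug, ka 0.7–3/h, sample 2 spread over 1, 2, 3 and 4 h, 35% delivering within 12 h | 30–59%; 142% in one set | 3–4% | data remove 1–16% of variance |
| 60 per drug, scheduled windows, no birth sample | 57–669% | 4–9% | shrinkage 45–91% |
| 60 per drug, four different site times | 30–409% | 4–5% | shrinkage 46–90% |
| 60 per drug, plus an assumed random birth sample | 23–344% | 4–5% | shrinkage 43–89% |

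The very large values come from sets where absorption and distribution are hard to separate. They mean that ka is close to inestimable and are not literal standard errors. With the scheduled windows, the ka estimate correlates 0.49 to 1.00 with V1 and −0.76 to −1.00 with Q.

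**What the ANOVA sees, and the true error.** With n women per drug, and taking RSE as the standard error of a log parameter:

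- ANOVA SE of the log difference ≈ 0.30 × √(fraction of variance removed) × √(2/n), which equals 0.30 × (1 − shrinkage) × √(2/n)
- actual SE of the log difference ≈ √2 × RSE

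For 100 women per drug: 0.30 × √0.01 to 0.30 × √0.16 = 0.03 to 0.12; times √(2/100) = 0.141, this gives 0.004 to 0.017. The actual SE is √2 × 0.30 to √2 × 0.59 = 0.42 to 0.83. Even the most lenient pairing, 0.42 / 0.017, is about 25-fold.

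Two matched cases with 60 women per drug, 15% residual error and the birth sample included, so that √(2/60) = 0.183:

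| Case | Parameter | RSE | Shrinkage | ANOVA SE | Actual SE | Ratio | Chance of p < 0.05 with no true difference |
|---|---|---|---|---|---|---|---|
| ka 2/h, Q 5 L/h (smallest ka RSE in the 60-women runs) | ka | 23% | 0.81 | 0.010 | 0.33 | 31 | 95% |
| | V1 | 7% | 0.21 | 0.043 | 0.099 | 2.3 | 39% |
| | CL | 4% | 0.04 | 0.053 | 0.057 | 1.1 | 7% |
| ka 1/h, CL 8 L/h | ka | 68% | 0.70 | 0.016 | 0.96 | 59 | 97% |
| | V1 | 54% | 0.34 | 0.036 | 0.76 | 21 | 93% |
| | CL | 4% | 0.03 | 0.053 | 0.057 | 1.1 | 7% |

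The last column is P(|Z| > 1.96 / ratio). For CL the ANOVA behaves almost as it should. For ka it does not, and for V1 it depends on the case.

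**What is not affected.** With 100 women per drug and no prior on ka, the typical woman's peak has an RSE of 3.4–9.4% after dose 1 and 3.3–7.7% after dose 4, and the 0–12 h AUC 2.5–3.1%. The time of the peak is 0.7–2.0 h in these sets, so sample 2 falls at or near it, and errors in ka, V1 and Q offset each other in the predicted profile.

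**The case against.** There are several fair points on the plan's side.

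- **Sparse sampling was a deliberate choice**, because dense sampling is impractical in these women, and population PK pools across them. That stands, but pooling is already in the calculation: it rescues CL and not ka.
- **ka appears only as an example**, and the ANOVA sentence does not name it. True, but that sentence directly follows the list of individual parameters and excludes none of them.
- **Between-subject variability is estimated only where feasible** (Random effect models), so the ka term may be dropped. Each woman's ka would then simply repeat her drug's typical value, leaving nothing to summarise or test.
- **The size rests on assumed PK values.** That stands. The site-specific schedules and the earlier study are not shown, and the runs differ widely. All of them agree that individual ka is poorly informed and CL well informed.

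A reader might also infer that simulated peaks and the PD models inherit the error in ka. The calculation does not support this: typical peaks are estimated to within 3–9% without any prior.

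Nor can it be said in general that the reported ka would rest on starting values. That applies only where the likelihood is nearly flat; elsewhere the data determine the estimate, if imprecisely.

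**Conclusion.** The point holds for the between-drug comparison of individual ka. Under the assumed values and 100 women per drug, the RSE of ka is roughly 30–60%, and above 100% when absorption and distribution half-lives are similar. A woman's data remove about 1–16% of the variance in her ka. An ANOVA on the individual values then understates the standard error about 25-fold or more, and in the matched cases it would declare a difference about 95% of the time when none exists. V1, and by the same mechanism Q, can be affected to a lesser and variable degree.

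CL, overall exposure and typical peaks are well supported, so the objective of describing the PK of the two regimens is not threatened. The article does not support a demand to redesign the sampling or to make an informative prior mandatory in the main analysis. One added draw at 0.33 h would bring the RSE of ka to 14–35% when ka is 2–3/h but leave it at 55–420% when ka is 0.5–1/h. A prior might also have to come from non-pregnant women.

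**What to change.** In Statistical analysis:

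1. Remove ka from the individual parameters tested by ANOVA.
2. Compare the drugs on weakly informed parameters only through the population estimates and their model-based 95% CIs, a comparison the section already plans. This covers ka, and V and Q where shrinkage or relative standard error is high.
3. Report shrinkage for every parameter that has a between-subject term.

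In Model building procedures, add one sensitivity analysis: refit with the earlier study's ka entered with its uncertainty as an informative prior and no between-subject term on ka, and show results with and without the prior. As an illustration, a prior with an assumed 15% standard error brings the RSE of ka to about 12–15%.

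The cost is a few sentences and one further model run; no sample is added or moved. The downside is that no individual-level comparison of ka is reported, and that the sensitivity run borrows ka from an outside population that may not be pregnant. Showing both fits makes that borrowing visible.

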### Sample collection and processing

The blood samples at each time point will be collected in different vials depending on the analysis required: fluoride vial for glucose, plasma preparation tube (K2EDTA; dipotassium ethylenediaminetetraacetic acid) for WBC total and differential counts and steroid levels of DEX and BET, and serum separating tube for serum cortisol. The blood samples for glucose and WBC counts will be sent to the hospital-specific laboratories and analysed within 1 hour of collection while maintaining them at room temperature (below 25°C) during the entire time.

The serum and plasma sample aliquots for cortisol and steroid assays will be sent for analysis to a central study laboratory at Syngene International, Bangalore, India. For the cortisol assay, serum will be stored in a freezer (−20°C) immediately after aliquoting. For steroid assay, 200 µL of sodium arsenate solution will be added to the K2EDTA vacutainer tube kept in an ice bath, and the 4 mL blood sample will be added to this vacutainer tube. The tube will be gently inverted 8–10 times for thorough mixing and centrifuged at 3500 rpm for 10 min at 4°C, within 30 min from blood sample collection to separate the plasma. The plasma will be divided into two aliquots in cryovials with pre-added sodium fluoride solution (50 µL for 1 mL plasma), and immediately stored in the freezer (−20°C) until shipment.

All sites will ship the primary aliquots for cortisol and steroid samples to the central laboratory in India on dry ice under temperature-controlled conditions to ensure timely analysis of the samples within the 90-day time window for which the stability testing is proven for the analysis methods used. Quality checks will be undertaken at various steps, and back-up samples will be requested by the central study laboratory in case the primary samples cannot be analysed for any reason.

### Laboratory analysis-bioanalytical methods

For PD parameters, total and differential WBC counts will be measured using automated analysers that use the electrical impedance methodology.^26^ Plasma glucose will be measured using the hexokinase method.^27^ Serum cortisol will be measured by a validated electrochemiluminescence immunoassay. Plasma concentrations of DEX and BET will be measured using a validated liquid chromatography mass spectroscopy methodology for calculating PK parameters.

### Quality assurance

Standard operating procedures will be prepared for all study procedures including maternal and cord blood sample collection, processing, storage and handling. The site teams will undergo hands-on training in blood sample collection and processing procedures at the central study laboratory in India, followed by a dry run at each hospital under the supervision of the central study laboratory team and WHO trial coordinating unit (TCU). Procedural details regarding sample collection and processing, for example, sample collection to storage time, sample analysis time for glucose and WBC count, addition of various solutions during PK sample processing, storage temperature, etc, will be maintained in the form of logs at all sites hospitals and reviewed every 2–4 weeks by the WHO TCU. Regular site monitoring visits will be made by WHO TCU and independent, external monitors.

### Data collection and management

In addition to the main trial data that includes date and time of each dose of ACS and date and time of birth, additional data will be collected on the date and time of each blood sample (maternal and cord blood), estimated gestational age at time of first dose of ACS administration, time of the last dose, maternal characteristics including: age, body weight, height, BMI and liver and renal function if clinically indicated, and possible covariates such as time last meal taken, and concomitant medications.

Data will be managed centrally by a data management team, supervised directly by WHO project managers. The study statistician will be responsible for the development of the statistical analysis plan and reporting to the DSMB. A web-based, Good Clinical Practice (GCP) compliant data management platform (Kamolo, Centro Rosarino Estudios Perinatales) will be used and will be overseen by the site data managers. All data will be collected in study centres on paper case report forms. Quality control will be performed at each site, and a validation system will be built into the data entry and management system to ensure consistency, accuracy and completeness of the data collected.

### PK-PD data modelling and analysis

#### Data screening

The measured drug concentration versus data will be initially graphed to determine consistency with PK expectations (declining concentrations after dosing) and to look for outliers. The PD will be grouped according to drug or placebo dosing for exploratory assessment of generally expected differences from baseline measurements.

#### Software

PK data and drug response PD data collected from the study will be modelled using NONMEM 7.5 (ICON Pic) software. For statistical analysis, graphics 4.3.2 (The R Project Group, www.r-project.org) will be used.

#### Estimation method

The first-order conditional estimation method with the interaction option implemented in NONMEM 7.5 will be primarily considered. Alternatively, the importance sampling method will be used for parameter estimation if the primary method fails due to sparse data.

#### Model building procedures

A base model will first be developed for the pretreatment and placebo measurements, the PK of each drug, and each PD biomarker using the models established by Krzyzanski *et al*.^28^ Once adequate base models have been developed, the joint drug/PD models and covariate effect models will be built. To ensure reasonable initial estimates, we will use the results from the Krzyzanski study.

#### Fixed effects models

At stage 1, a two-compartment disposition model with first-order absorption will be used for describing plasma drug concentrations as the primary assessment (figure 2). Placebo cortisol data will be captured with the cosine circadian model. The inhibitory effect of the drugs on cortisol will be described by an indirect response model (figure 2).^29^ The cellular PD biomarkers will be described by inhibitory or stimulatory indirect response models that account for production (*k*_in_) and loss (*k*_out_) of the various biomarkers. Drug effects on plasma glucose will be described by a similar basic stimulatory indirect response model.

**Figure 2 F2:**
[figure not shown]
Schematic diagram of a PK-PD model describing DEX and BET plasma concentrations in pregnant women and their alteration of assessed biomarkers following multiple intramuscular dose administrations. BET, betamethasone; DEX, dexamethasone; PD, pharmacodynamics; PK, pharmacokinetics.

At stage 2, we will expand our meta-analysis of all available PK data for DEXp and BETp using a minimal physiologically based PK (mPBPK) model^30^ to compare the PK of these drugs in the current study. These drugs have linear PK that facilitates such comparison. An exploratory assessment will be made to determine whether it will be feasible to incorporate the designated covariates and consider the maternal PD in the mPBPK model.

#### Random effect models

The between-subject variability will be estimated for all parameters where feasible. A log-normal parameter variability model or other appropriate parameter variability models will be considered for the PK and PD parameters. For the residual unidentified variability, additive, proportional and a combined additive and proportional error models will be considered.

#### Covariate model

The subject population is a heterogeneous group of women but with limited age ranges. The broad protocol inclusion and exclusion criteria will create considerable inter-subject variability. Assessment of covariate effects such as race and body weights may be possible under these conditions.

#### Model performance diagnostics

Standard methods for diagnostics of model performance will be applied. These will include the value of the objective function, observed versus prediction plots, weighted residuals versus time and prediction plots and visual predictive checks.

#### Simulations

Simulations of model PK/PD variables will be performed to examine the data and model fittings in comparison to the expectations of previous PK/PD modelling of corticosteroids at higher doses in healthy and pregnant women.^28^,^30^

#### Statistical analysis

Drug-related PK and PD individual parameters (eg, V, CL, ka, Emax, EC50) will be summarised using descriptive statistics. Two-way analysis of variance will be applied to test for between drug differences. The population estimates of PK-PD parameters will be compared using 95% CIs. For the model selection, the χ^2^ test for significance of the change in the maximum likelihood objective function will be used. For the selection of significant covariates, the likelihood ratio test will be applied.

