### Study design

The PK-PD study will be nested within the ACTION-III trial (figure 1). The ACTION-III trial enrols women with singleton or multiple pregnancy at 34 weeks 0 days to 36 weeks 5 days of gestation, with at least one live foetus, and a high probability of late preterm birth defined as birth expected between 12 hours and 7 days after randomisation. Women with clinical suspicion or evidence of clinical chorioamnionitis or severe infection, those having received any systemic corticosteroid outside of trial in the previous 2 weeks, no ultrasound assessment of gestational age, major or lethal congenital fetal anomaly, participating in another clinical trial, or having previously participated in any ACTION trial or having any contraindication to corticosteroids are excluded.^5^ Women consenting to participate in the ACTION-III trial are randomised in a 1:1:1 ratio to receive the investigational medicinal product (IMP), which could be any one of the three treatments as follows: (1) DEXp 6 mg intramuscularly 12 hourly for four doses (currently recommended dose) or (2) BETp 2 mg intramuscularly 12 hourly for four doses (lower dose) or (3) placebo. A single course of IMP is administered every 12 hours, to a total of four doses or until birth occurs, whichever occurs first. Enrolment into the PK-PD study: all women randomised into the ACTION-III trial at the selected participating hospitals will be assessed for eligibility for the PK-PD study, and if eligible (criteria listed below), will be enrolled in the PK-PD study following a written, informed consent.

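### The between-drug ANOVA on individual Emax and EC50 ignores the uncertainty in each drug's typical value, which may be large with one dose level per drug and sparse PD sampling

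*Protocol article*

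**What the plan says.** Under Study design, women are "randomised in a 1:1:1 ratio to receive the investigational medicinal product (IMP", with active arms "DEXp 6 mg intramuscularly 12 hourly for four doses (currently recommended dose) or (2) BETp 2 mg intramuscularly 12 hourly for four doses". Dosing continues "to a total of four doses or until birth occurs, whichever occurs first", so the number of doses varies between women, but the amount per dose within a drug does not.

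Table 1 (Study procedures) schedules maternal PD samples at baseline, 1–4 hours and 8–12 hours after the first dose, and then at 24–36, 48–60 and 72–96 hours after the last dose. The birth sample has no maternal PD measurement.

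Under Fixed effects models, "The cellular PD biomarkers will be described by inhibitory or stimulatory indirect response models". Glucose is treated similarly, and cortisol by an inhibitory indirect response model. Model building procedures uses earlier published results as initial estimates.

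Under Statistical analysis, "Drug-related PK and PD individual parameters (eg, V, CL, ka, Emax, EC50) will be summarised using descriptive statistics". The next sentences apply a two-way ANOVA for differences between drugs, compare population estimates by 95% confidence intervals, and use likelihood-based tests for model and covariate selection.

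**The concern.** Within each drug the amount per dose never changes, so Emax can be separated from EC50 only through the rise and fall of concentration in each woman and the assumed form of the model. If EC50 is close to or above the highest concentration reached, many pairs of Emax and EC50 fit about equally well and mainly their ratio is estimated.

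The ANOVA makes this worse. Individual estimates from a population model are centred on the fitted typical value for that drug. An error in that value moves every woman in the arm together, yet the ANOVA sees only the spread between women. It can therefore report a difference in potency or maximum effect between DEX and BET that is nothing but estimation error.

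The listed diagnostics (objective function, prediction and residual plots, visual predictive checks) can look good while two parameters are collinear. The Abstract also promises to study optimal dosing by Monte Carlo simulation. Predicting response at other doses needs Emax and EC50 separately.

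**Working it through.** **1. The plan's own figure.** Sample size asks for 30 women with complete samples and recruits 50 per arm per country. 30/(1 − 0.40) = 50 reproduces this (a literal 60% increase gives 30 × 1.6 = 48). With 40% loss, 50 × 0.60 = 30 per arm per country, or 60 per drug over two countries. The section justifies this number by covariate associations with PK parameters. It gives no precision target for a PD parameter.

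**2. When PD is observed.** Four 12-hourly doses fall at 0, 12, 24 and 36 h. PD samples then fall at 1–4 and 8–12 h, next at 36 + 24 = 60 to 36 + 36 = 72 h, then at 84–96 and 108–132 h. Nothing is scheduled between 12 and 60 h, which covers the peaks of doses 2 to 4.

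**3. Can Emax and EC50 be separated?** I used first-order population Fisher information, F = Σ N J′V⁻¹J with V = JΩJ′ + σ²I, parameters on the log scale and 60 women per drug. Assumptions, none from the document:
- PK known: ka 2/h, V 70 L, half-life 5 h (DEX) and 9 h (BET), peaks about 88 and 41 ng/mL.
- PD: Emax 0.95 with kout 0.5/h (inhibition), or Emax 1.0 with kout 0.2/h (stimulation).
- 30% between-subject SD, 20% residual error, no circadian term, four doses.

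SE of the log ratio = √(SE²DEX + SE²BET). The 95% CI multiplies and divides the ratio by exp(1.96 × SE).

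| Model, EC50 (ng/mL) | SE log EC50 DEX / BET | Emax–EC50 correlation DEX / BET | SE of log ratio | CI factor | CI factor, Emax known |
|---|---|---|---|---|---|
| Inhibition, 3 | 0.11 / 0.12 | 0.23 / 0.39 | 0.16 | 1.4 | 1.4 |
| Inhibition, 30 | 0.57 / 0.96 | 0.98 / 0.99 | 1.12 | 9 | 1.4 |
| Stimulation, 3 | 0.58 / 0.40 | 0.88 / 0.78 | 0.70 | 4 | 2.1 |
| Stimulation, 10 | 0.95 / 0.88 | 0.97 / 0.97 | 1.30 | 13 | 1.8 |

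The matrix could be inverted in all 24 scenarios run (two drugs, two effect types, EC50 from 1 to 300), so the parameters are structurally identifiable. At EC50 of 100 or more the SE of log EC50 exceeds 2 throughout. BET is the less precise arm at EC50 of 30 and above, but not in the stimulation rows at 3 and 10.

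**4. How much does sharing parameters help?** This second set of assumptions takes peaks of 83 and 38 ng/mL, half-lives of 4.5 and 8 h, kout 0.5/h, Emax 0.6 (stimulation) or 0.95 (inhibition), and 15% residual error. Between-subject SD is 15% on baseline, 30% on EC50 and, for stimulation, 30% on Emax. Half the women receive four doses, a quarter three and a quarter two. SE of the log EC50 ratio at EC50 = 1 / 5 / 20 ng/mL:

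| | Stimulation | Inhibition |
|---|---|---|
| Nothing shared | 0.39 / 0.54 / 1.37 | 0.10 / 0.17 / 0.57 |
| Baseline and kout shared | 0.32 / 0.41 / 0.86 | 0.08 / 0.13 / 0.33 |
| Emax shared too | 0.31 / 0.32 / 0.35 | 0.07 / 0.08 / 0.12 |

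With lower assumed peaks (64 and 21 ng/mL) the stimulation rows become 0.41 / 0.69 / 2.4, then 0.33 / 0.50 / 1.47, then 0.31 / 0.32 / 0.42.

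**5. What the ANOVA would use.** With 30% between-subject SD in log EC50, its SE is at most √(0.30²/60 + 0.30²/60) = 0.055, and smaller if individual estimates shrink. It declares a difference at |log ratio| > 1.96 × 0.055 = 0.107. If the drugs are truly equal, the false-positive rate is 2[1 − Φ(0.107/SE)]:
- SE 0.08: 0.107/0.08 = 1.34, rate 18%.
- SE 0.10: 1.07, rate 28%.
- SE 0.54: 0.20, rate 84%.
- SE 1.37: 0.08, rate 94%.

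So even a well-estimated biomarker exceeds a nominal 5%, and a poorly estimated one is almost sure to show a difference.

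**The case against.** Several points on the other side stand.

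- A reader might infer that one dose level leaves the data unable to tell Emax from EC50. That is too strong. Concentrations vary widely within each woman, the PD models are driven by concentration, and for a strong inhibitory effect with EC50 well below the peak the precision is good.
- A reader might also infer that drug and dose are confounded in every listed parameter. They are not. Under the linear PK stated in the stage 2 modelling text, V, CL and ka do not depend on dose, and EC50 is in concentration units, so the dose difference enters through exposure. Only model-free contrasts of the DEX and BET arms mix drug with dose, and the article mostly speaks of regimens already.
- The article does not say that baseline and turnover are fitted afresh for each drug. The middle row of the second table may therefore be nearer the intended analysis, and part of the gain from sharing has nothing to do with Emax.
- The comparison of population estimates by 95% confidence intervals does carry estimation error. It stands beside the ANOVA, however, and the two can disagree with no rule for which prevails.
- A common Emax is itself an assumption, and the fit that relaxes it is the imprecise one. Failing to reject it is weak evidence where Emax is poorly estimated.

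Parameter sharing and fallbacks may well be set out in an analysis plan not shown here, and their absence from the article is not the point. The ANOVA is a stated choice, and the article already contains the better tool, the likelihood ratio test.

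**Conclusion.** The point holds in a limited form. The fault is the use of a two-way ANOVA on individual PD parameters to test for drug differences. I read the ANOVA sentence as applying to the individual parameters named just before it.

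Under the assumptions shown, its SE is too small by a factor of about 1.5 (0.08/0.055) to 25 (1.37/0.055), giving false-positive rates of roughly 20% to 95%. The damage is greatest for biomarkers whose EC50 is near or above the peak concentration. There Emax and EC50 are almost collinear, usually more so for BET.

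The document gives no EC50, Emax, turnover rate, volume or peak concentration, so every precision figure is conditional. The figures are also optimistic: PK is treated as known, the circadian term is left out and samples are complete. The direction does not depend on them, because an ANOVA on individual estimates leaves out the error in each typical value whatever the EC50.

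**What to change.** In Statistical analysis, keep the descriptive summaries and change the test for PD parameters:

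1. Replace the two-way ANOVA with one joint model per biomarker, fitted to DEX, BET and placebo women together, with common baseline and turnover (kin, kout).
2. Test a drug-specific against a common EC50 by likelihood ratio test. Keep Emax (Imax) common where the objective-function test does not reject it.
3. Show the fit with separate Emax, with its standard errors, as a sensitivity analysis, so that readers can see how much rests on the common value.
4. Do not test Emax between drugs where its relative SE is large.
5. Describe raw DEX versus BET contrasts in glucose, cell counts or cortisol as differences between regimens.

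The cost is a few sentences, slightly more modelling work and a common-Emax assumption for some biomarkers. No change to recruitment, sampling or treatment is needed.
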